### **6.2.2 Screening visit**

- Signature of Informed Consent Form.
- Checking inclusion and exclusion criteria.
- Demographics and general medical history.
- Lumbar related medical history (includes past history of osteoarthritis, osteoporosis, lumbar pain, injury, trauma, fractures, surgical procedure or other conditions).
- Medication history therapy and unresponsive (including physical therapy) for at least 6 months.
- Vital signs after sitting for at least 5 minutes, (temperature, blood pressure, and heart rate, height, weight).
- Musculoskeletal physical exploration.
- Lumbar spine examination (X ray).
- Pain assessment of the lumbar spine by visual pain scale (VAS, Oswestry Disability Index ODI in order to measure a patient's permanent functional disability, Quality of life assessment using SF-36.
  - Instruction for wash out (NSAIDS washout of at least 2 days before the screening Visit, no painkillers 24h before the screening visit) will be given to the patient after written informed consent.
- If clinical and radiological criteria fulfilled, perform ECG (12-lead)
- Blood sampling for routine laboratory testing
  - Haematology: haematocrit, haemoglobin, RBC, WBC; PC
  - Biochemistry: Electrolytes, Creatinine, BUN, ALT, AST, AP, Bilirubin, Coagulation (INR, PTT)
  - CRP
- Urinalysis (dipstick): Glucose, Ketones, blood, protein, nitrite, leucocytes, , bilirubin in urine
  - Urine pregnancy test in woman of childbearing

potential

- Blood sampling for preceptive viral serologies
  - HBs antigens
  - Anti-HBc antibodies
  - Anti-HCV antibodies
  - Anti-HIV-1 and anti-HIV-2 antibodies, Anti HV1 gp41
  - Anti-HTLV-1, HTLV-2 antibodies
  - Wasserman testing
  - Blood testing for Syphilis serology
- Concomitant medication

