#### **3.1 Inclusion criteria**

- Age between 18 and 65 years.
- Signed informed consent.
- Symptomatic chronic LBP due to moderate IDD [modified Pfirrmann score 3-4 (Pfirrmann et al., 2001), Griffith score 3-7(Griffith et al., 2007)] at max.3 levels of the lumbar spine unresponsive to conservative treatment, physical and medical for at least 6 months. Physical treatment includes physiotherapy. Medical treatments includes NSAID, paracetamol, opioids and myorelaxant. (For more details, see paragraph 1.1.4).
- Annulus fibrosus intact, demonstrated by MRI.
- Pain baseline > 40 mm on VAS (0- 100).NSAID washout of at least 2 days before screening.
- NSAID washout of at least 2 days before screening.

- Painkillers washout of at least 24 hours before screening.
- For females of childbearing potential (see definitions in paragraph 6.5), a negative pregnancy test must be documented at Screening.
- Men and women should use effective contraception during treatment and for at least 24 months after BM-MSD discontinuation. The complete list of contraceptive methods is described in the patient information sheet and in the paragraph 6.5. As a precautionary measure, breast-feeding should be discontinued during treatment with BM-MSD and should not be restarted after discontinuation of BM-MSD.

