| Checking inclusion and exclusion criteria                           |                | X           |                             |                  |                       |                       |            |             |              |              |
| Randomization                                                       |                |             | X                           |                  |                       |                       |            |             |              |              |
| Pain lumbar spine (VAS), ODI, SF-36                                 | X              | X           |                             | X                | X                     | X                     | X          | X           | X            | X            |
| Lateral MRI, T2, quantitative                                       | X d |             |                             |                  | X                     |                       |            | X           | X            | X            |
| Adverse Events                                                      |                |             |                             |                  | X                     | X                     | X          | X           | X            | X            |
| Concomitant medication                                              |                | X           |                             | X                | X                     | X                     | X          | X           | X            | X            |

a: NSAIDs washout of at least 2 days before screening, inclusion and baseline. NSAIDs will not be authorized during the first 6-month after baseline. However, if needed after the first 6 months, NSAIDs could be used

b: Patients will be required to refrain from taking paracetamol or opioids within 24 hours of each clinical visit for efficacy evaluations

c: vital signs: Temperature, heart rate, arterial blood pressure, height, weight

d: MRI was also used to assess the Pfirrmann and Griffith's score

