## **6.2 Visits during the course of the trial**

### **6.2.1 Pre-Screening visit**

- Delivery of the Information sheet.
  - Lateral MRI, T2, quantitative.
  - Pain assessment of the lumbar spine by visual pain scale (VAS, Oswestry Disability Index ODI in order to measure a patient's permanent functional disability, Quality of life assessment using SF-36.

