## **13 Informed Consent, Ethical Review, and Regulatory Considerations**

### **13.1 Informed consent**

Informed consent must be obtained from each subject, before the performance of any study-related activity.

The investigator or an authorized associate must explain the nature of the study and the treatment in such a manner that the subject is aware of his/her rights and responsibilities, as well as potential benefits and risks. The investigator is also responsible for answering any questions the subject may have throughout the study and for sharing any new information, in a timely manner, that may be relevant to the subject's willingness to continue his/her participation in the study. The Informed Consent Form (ICF) and Patient Information Leaflet (PIL) also include indications about the insurance coverage and the resulting regulations for the delimitation of damages. The subject will be informed that he/she should notify the investigator of any other medical measures during the study period and that he/she cannot simultaneously take part in another study.

Subjects must also be informed that participation is voluntary and that they may withdraw from the study at any time, without prejudice to their current or future care. Documentation of the discussion and the date of informed consent must be recorded in the subject's medical record.

Concerning the study data, by signing the ICF, the patient will accept that the study data may be examined by the Sponsor, the CAs, ECs, a mandated auditor and/or the study monitor in compliance with the statement of confidentiality.

Subjects or legal representative must sign and date the ICF after the nature of the study has been fully explained. A copy of the completed ICF as well as the PIL must be provided to the subject. Before its use, the PIL and ICF must meet local regulations and be approved by the EC

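### The schedule puts the pre-screening MRI and questionnaires before consent, and first gives the washout instruction at the visit the washout should precede

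*Protocol*

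**What the plan says.** **Consent.** Protocol 13.1 sets the rule: "Informed consent must be obtained from each subject, before the performance of any study-related activity". The pre-screening visit (6.2.1; Day -60/-46 in 6.1) lists "Delivery of the Information sheet", then "Lateral MRI, T2, quantitative", then VAS, ODI and SF-36 under "Pain assessment of the lumbar spine by visual pain scale". The item "Signature of Informed Consent Form" appears only at the next visit, screening (6.2.2; Day -45/-41). Footnote d to the schedule, attached to the pre-screening MRI, adds "MRI was also used to assess the Pfirrmann and Griffith's score". Both scores are part of the inclusion criteria in 3.1.

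**Washout.** Section 3.1 requires "NSAID washout of at least 2 days before screening" and a painkiller washout of at least 24 hours before screening. In 6.1 the washout instructions are first marked in the screening column, with nothing at pre-screening. Section 6.2.2 describes an instruction about the period before the screening visit and says that it "will be given to the patient after written informed consent". VAS, ODI and SF-36 are collected and the criteria are checked at that same visit.

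**Later visits.** Section 6.2.3 confirms the criteria and then randomises. Footnote a requires NSAID washout before screening, inclusion and baseline. Footnote b covers paracetamol and opioids before clinical visits for efficacy evaluations. In 6.1 the inclusion column carries neither a VAS nor a washout instruction.

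**The concern.** Two ordering problems arise from the same pair of visits.

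First, if the pre-screening procedures are study-related, the visit order conflicts with 13.1. A site that follows the schedule exactly will collect trial data before consent.

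Second, the pain criterion (VAS above 40 mm) is meant to be judged on a washed-out patient. If the washout instruction comes only once the patient is already at screening, the protocol itself does nothing to bring that about. The population must have failed at least 6 months of conservative treatment, and 3.1 counts NSAIDs, paracetamol and opioids among the medical treatments, so analgesic use at screening is plausible. At stake are the validity of consent for the first data collected, two inclusion criteria whose fulfilment is left to chance, and a pain-eligibility score that may not mean the same thing in every patient.

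**Working it through.** No sample-size or power formula applies. The check uses the visit windows in 6.1 and compares the texts.

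**Inputs (6.1)**
- Pre-screening: Day -60 to -46
- Screening: Day -45 to -41
- Inclusion and randomisation: Day -45 to -31
- Washout required before screening (3.1): at least 2 days for NSAIDs, at least 24 hours for painkillers

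**Step 1. Delay from pre-screening procedures to consent** (screening day minus pre-screening day)
- Shortest: -45 - (-46) = 1 day
- Longest: -41 - (-60) = 19 days

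The delay is always positive, so no permitted combination of dates puts consent first.

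**Step 2. Are the procedures study-related?** The document points that way. Section 6.2.1 stands under the trial's visits. Footnote d uses the MRI for scores in the inclusion criteria, and no MRI is marked at screening or inclusion, so MRI eligibility rests on this scan. Quantitative MRI is a secondary endpoint technique (2.4.2), and VAS, ODI and SF-36 are trial outcomes. Nothing calls these procedures routine care, and no separate pre-screening consent is described.

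**Step 3. Lead time of the washout instruction.** The instruction follows consent, and consent is signed at screening. The lead time to that visit is therefore 0 days, against 2 days and 24 hours required.

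**Step 4. Could the screening window absorb it?** Its width is -41 - (-45) = 4 days, so consent on one day and measurement at least 2 days later would fit. Section 6.2.2 describes one visit and no such split.

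**Step 5. Does a later visit before randomisation repair it?** Inclusion follows screening by 0 days (both on Day -45) to -31 - (-45) = 14 days. The criteria are confirmed there and footnote a asks for NSAID washout, but no VAS is scheduled, so no new pain score is produced. The Day 0 VAS and ODI do have washout listed (6.2.5), but Day 0 comes after randomisation.

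**The case against.** **The consent conflict needs the procedures to be study-related.** Section 1.1.2 describes MRI as part of diagnosis, and footnote d could describe reuse of an existing scan. This has some force for the MRI, although the document never says so. It does not reach the three questionnaires.

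**A reader might infer that the washout criteria can never be met, and that all 52 patients are affected.** The documents do not support that. Section 3.1 asks for a state, namely no NSAID for 2 days and no painkiller for 24 hours. It does not require that the patient stopped on instruction. A patient not taking these drugs, or who stopped unprompted, qualifies. The text of the information sheet handed over at pre-screening is not shown, and an undescribed split of screening would also work. What stands is narrower: the scheduled instruction does not secure the criterion.

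**There is a check before randomisation.** This is true and should be acknowledged, but without a VAS or a washout instruction at inclusion it is only a partial safeguard.

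**A reader might also infer bias in the efficacy result.** Response is measured against baseline, and VAS and ODI are taken again at Day 0 with washout listed. The documents do not support a direct effect on the primary comparison.

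**Conclusion.** The point holds as an internal contradiction with limited reach.

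- **Consent:** as scheduled, four procedures (MRI, VAS, ODI, SF-36) precede consent by 1 to 19 days, in conflict with 13.1, for all 52 planned patients. This assumes that they are study-related, which the document supports but does not state.
- **Washout:** the instruction has no lead time before the visit it refers to. It fails to secure two inclusion criteria for patients taking NSAIDs or painkillers shortly before screening. The documents give no number for this group. For these patients the VAS used for eligibility may be taken on analgesics. This assumes that the pain criterion is judged on the screening VAS, which is where 6.2.2 places the check.
- **Reach:** consent documentation and eligibility. Day 0 measurements are not affected by this ordering.

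**What to change.** Move the consent signature to the start of pre-screening, before the MRI and questionnaires, and give the existing washout instruction there once consent is signed. Reconcile 3.1, 6.1 (with footnotes a and b), 6.2.1, 6.2.2 and 13.1 accordingly. The washout lengths and the drugs covered need not change for this purpose.

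One detail needs attention. The present windows allow pre-screening on Day -46 and screening on Day -45, a gap of 1 day, which is shorter than the existing 2-day NSAID requirement. The schedule should ensure that the interval between the visits accommodates the washout already stated.

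Leaving the instruction where it is and relying on footnote a at the inclusion visit would not be enough. That footnote covers NSAIDs only, and no VAS is scheduled at inclusion.

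The cost is wording in the schedule and consent procedure, plus an earlier consent discussion: 15 days earlier if each visit falls on the first day of its window, and 1 to 19 days across all permitted dates. Patients who fail on the pre-screening MRI will also have been through consent.

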### **6.2.3 Inclusion visit and randomization**

- Confirm inclusion and exclusion criteria
- Randomization

Randomization procedure: the randomization is performed 24 hour-a-day online by the central randomization web-service customized by the sistem. To randomize a patient, investigators have to login, enter the patient identification, additional checks and factor values. The person in charge of cell injections will be strictly forbidden from discussing treatment allocation with patients and clinical observers.

### **6.2.4 BM-MSc Withdrawal**

#### **- Prior to Bone Marrow cells extraction:**

- Physical exploration
- Vital signs (Temp, BP, HR)
- Blood sampling for routine laboratory testing

Haematology: haematocrit, haemoglobin, RBC, WBC; PC

Biochemistry: Electrolytes, Creatinine, BUN, ALT, AST, AP, Bilirubin, CRP

- Urinalysis (dipstick): Glucose, Ketones, blood, protein, nitrite, leucocytes, bilirubin in urine

- Pain assessment of the lumbar spine by visual pain scale (VAS, Oswestry Disability Index in order to measure a patient's permanent functional disability, Quality of life assessment using SF-36
- An antibiotic prophylaxis will be performed. The prophylaxis is the following: 2g Cefazolin, 1/2 hour before injection. Or in case of allergy: Clindamycin 900 mg (1/2 h before injection). The antibiotic solution is to be delivered intravenously (IV).
- Concomitant medication (analgesic medication with diary file)

### **Bone Marrow Cell extraction procedure**

The surgical procedure is described in section 5.3

### **After Bone Marrow Cell extraction procedure**

After completion of the BM extraction procedure subjects are monitored for vital signs for 2 hours and they will have an authorization to leave the investigation centre after a last check by the investigator.

Prior to discharge a physical examination of the subject and AE recording is performed by the investigator.

A second visit 2' equivalent to the visit 2 will be done if a problem occurs as cells contamination shipping problem, not enough cells after the first bone-aspiration.

### **6.2.5 Day 0 - Visit 0: Visit baseline and treatment**

- Physical exploration
- Vital signs (Temp, BP, HR)
- Lateral MRI, T2, quantitative
- Medication history therapy
- Blood sampling for routine laboratory testing
- Urine analysis

- Pain assessment of the lumbar spine by visual pain scale (VAS)
- Oswestry Disability Index in order to measure a patient's permanent functional disability, Quality of life assessment using SF-36
- Instruction for wash out (NSAIDS washout of at least 2 days before this screening Visit, no painkillers 24h before the visit)
- Prohibition of NSAIDs
- Adverse event assessment
- Concomitant medication
- Intervention : injection of autologous cells or sham procedure (under fluoroscopy guide and monitor cell implantation). The affected disks (max 3) are treated simultaneously once only, at the V0 visit and no subsequent doses are expected.

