## **2.4 Endpoints**

### **2.4.1 Primary Endpoint:**

- To evaluate the efficacy of intradiscal injection of autologous BM-MSC using the visual analog scale (VAS) and functional status assessed by the Oswestry disability index (ODI) after 24 months of treatment, defining

responders in case of at least 40% improvement in VAS or ODI at month 24 compared to baseline.

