## **4. Measurement of outcomes**

### **4.1 Primary Outcome Measures:**

The clinical response is defined as pain relief of at least 40% and 40 mm decrease on VAS scale between baseline and month 24, or 40% improvement of functional index ODI at month 24 compared to baseline. Chronic LBP is assessed using the VAS pain scale (0 – 100, where 0 represents no pain and 100 represents the worst pain imaginable). ODI scale ranges from 0 to 50 and allows evaluation of disability (0% – 20%: minimal disability; 20% – 40%: moderate disability; 40% – 60%: severe disability; 60% – 80%: crippled; 80% – 100%: bed-bound or exaggerating their symptoms).

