### **5.2 Methodology for obtaining bone marrow autologous**

Patient positioning: the patient is in prone position. Bone marrow (BM) is harvested from the posterior superior iliac crest region. Monitored anesthesia (conscious sedation) and local anesthesia will be used. After palpation of the bony landmarks, the procedural site is sterilely prepared and widely draped to ensure an adequate field.

Bone Marrow Aspiration: A Jamshidi needle is used. The skin is then injected down to and including the periosteum with 1% lidocaine without epinephrine. Then, the bone marrow aspiration trochar and needle are percutaneously inserted through the skin and subcutaneous tissues until it reaches the posterior iliac crest. Then, manual pressure is used to position the bone marrow aspiration trochar against the dense cortical bone, centering it over the middle of the posterior crest cortical walls. After the trochar is inserted into the posterior iliac crest but prior to aspiration, 1 mL of heparin (1,000 U/mL) will be preloaded into the syringe. Approximately 20 mL of bone marrow is aspirated, by using two 20-mL syringes. At conclusion a sterile dressing is applied.

The transport container with the raw material, is delivered to the manufacturer. Upon arrival, the container is inspected and the specimen is taken out to the clean-room

for processing. The duration of transport and temperature is recorded. Coherence with accompanying documents is controlled, including donor identifiers.

The sham procedure will consist of the same setting and instruments. The Jamshidi needle will be percutaneously inserted through the skin and subcutaneous tissues and not inserted in the posterior crest .

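### The primary endpoint names no baseline visit, and its likeliest reading (Day 0) falls after randomisation and after a marrow harvest that enters bone only in the cell arm

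*Protocol*

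**What the plan says.** Protocol section 2.4.1 defines "responders in case of at least 40% improvement in VAS or ODI at month 24 compared to baseline". Section 4.1 states the VAS route as "pain relief of at least 40% and 40 mm decrease on VAS scale between baseline and month 24", with a 40% ODI improvement as the alternative. Neither section names the visit that supplies the baseline.

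Section 6.2.5 is headed "Day 0 - Visit 0: Visit baseline and treatment", and VAS, ODI and SF-36 are taken there. Footnote a to table 6.1 lists separate time points: "NSAIDs washout of at least 2 days before screening, inclusion and baseline". Table 6.1 puts both randomisation and bone-marrow withdrawal at Day -45 to -31.

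Section 5.2 describes the two versions of the marrow procedure. In the cell arm the trocar enters the posterior iliac crest and "Approximately 20 mL of bone marrow is aspirated, by using two 20-mL syringes". In the sham arm "The Jamshidi needle will be percutaneously inserted through the skin and subcutaneous tissues and not inserted in the posterior crest".

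VAS, ODI and SF-36 are also collected earlier: at pre-screening, at screening, and at the bone-marrow visit under the heading "Prior to Bone Marrow cells extraction" (section 6.2.4).

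**The concern.** Response is a change relative to baseline, so the baseline should be measured before the arms are treated differently. If it is Day 0, it follows a randomised procedure that is invasive to bone in one arm only, at a site close to the region being scored. Residual harvest pain or disability at Day 0 would inflate the cell arm's starting value. By month 24 that component would presumably have gone, and its disappearance would be credited to the cells. Any such error runs in one direction, towards the product. It could enter through VAS or ODI and would also touch the secondary change-from-baseline analyses of ODI and SF-36.

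A repeat extraction (section 6.2.4) adds to the exposure. Its triggers are contamination, a shipping problem or too few cells. These can arise only where marrow is really taken, and the protocol states neither a day window nor a sham counterpart.

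**Working it through.** The protocol gives no figure for this bias, so there is none to reproduce. The timing can be checked exactly; the size can only be illustrated.

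**Which visit is baseline?**
- For Day 0: the title of section 6.2.5; the table 6.1 column that pairs baseline with treatment; footnote a, which separates baseline from screening and inclusion and counts the six-month NSAID restriction from baseline.
- For another reading: section 3.1 uses baseline for the pain entry criterion (above 40 mm), which is checked before randomisation. The safety part of section 4.2 uses screening results as baseline values, though VAS and ODI are not named in its list.
- Result: Day 0 is the natural reading but not a stated rule.

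**Timing.** Randomisation and harvest are at Day -45 to -31, so each precedes Day 0 by 31 to 45 days. Harvest pain must last at least 31 days to matter on the planned schedule. After a repeat harvest no window is given; the culture of about 21 days (section 5.1) still lies between harvest and injection.

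**Direction.** Let B be the undisturbed baseline and d the rise at Day 0 from the harvest. A 40% fall from the recorded value B + d needs a month-24 value of at most 0.6(B + d). The true improvement that is enough is 1 − 0.6(B + d)/B. With B = 60 mm:
- d = 2: 1 − 0.6 × 62/60 = 38%
- d = 5: 1 − 0.6 × 65/60 = 35%
- d = 10: 1 − 0.6 × 70/60 = 30%

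The same algebra applies to ODI on its own scale. Both VAS rules can flip with d = 5:
- Section 2.4.1 (40%): a month-24 VAS of 38 is 22/60 = 36.7% below 60 (non-responder) but 27/65 = 41.5% below 65 (responder). Under section 4.1 this patient fails either way, because 27 mm is less than 40 mm.
- Section 4.1 (40% and 40 mm): a month-24 VAS of 22 is 38 mm below 60 (non-responder) but 43 mm below 65 (responder).

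**Hypothetical size.** All of the following is assumed except the 30% rate and the 26 per arm, which come from section 7:
- no treatment effect, and a true response rate of 30% in both arms;
- VAS route only, although section 7 gives 30% as the overall responder rate;
- Day 0 VAS normal, restricted to above 40 and up to 100 mm;
- d added to the cell arm's baseline only;
- pooled z test of two proportions, critical value 1.96.

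Entries are the cell-arm response rate, with the chance of a false result favouring cells in parentheses.

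| Baseline mean/SD, change SD (mm) | Rule | d = 0 | d = 2 | d = 5 | d = 10 |
|---|---|---|---|---|---|
| 60/12, 20 | 40% | 30.0% (2.8%) | 32.1% (3.9%) | 35.3% (6.5%) | 40.9% (13.5%) |
| 60/12, 20 | 40% and 40 mm | 30.0% (2.8%) | 33.6% (5.0%) | 39.2% (11.0%) | 49.0% (29.8%) |
| 65/15, 25 | 40% | 30.0% (2.8%) | 31.7% (3.7%) | 34.2% (5.7%) | 38.5% (10.1%) |
| 65/15, 25 | 40% and 40 mm | 30.0% (2.8%) | 32.8% (4.5%) | 37.2% (8.6%) | 44.8% (20.5%) |

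The table shows sensitivity to d. It is not evidence that d differs from zero. ODI and SF-36 were not simulated.

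**The case against.** The strongest reply is that two links in the chain are missing from the protocol. First, it never says that the endpoint uses the Day 0 score, and a SAP may name the baseline visit. Second, nothing supports harvest pain that lasts 31 days or more, shifts a whole arm's mean, and is reported as lumbar pain. The aspirate is about 20 mL under local anaesthesia and sedation, patients leave after two hours of monitoring, and section 8.3 does not list harvest pain among expected reactions. Both points stand. They limit what can be claimed about size, but they do not put the baseline before the unequal procedure, and the protocol's own labels lead an analyst to Day 0.

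Two objections to the remedy also have force. The pre-extraction score may itself follow randomisation, since both share one window and randomisation comes first in the visit sequence. That is true, but the score still precedes the unequal procedure. Also, Day 0 matches month 24 on analgesic washout, while the bone-marrow column of table 6.1 has no washout mark. This applies to the bone-marrow score but not to screening, where washout is marked.

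A reader might infer that the trial's false-positive rate is known to be inflated. The documents do not support that: every figure above d = 0 depends on an assumed shift.

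**Conclusion.** The point holds as a should-fix. The baseline of the primary endpoint is tied to no visit. Its likeliest reading lies 31 to 45 days after randomisation and after a procedure that enters bone only in the cell arm. Any residual harvest effect would favour the product. Its size is unknown: nil if no harvest pain remains at Day 0, small at 2 mm (about 2 to 4 percentage points on a 30% rate under the assumptions above), and material at 10 mm (about 9 to 19 points).

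It would go too far to say that the protocol fixes Day 0 as the efficacy baseline, or that the bias is locked in. The first is an inference, and the second is wrong because pre-harvest scores are already collected.

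**What to change.** In sections 2.4.1, 4.1 and 6.1, name one pre-harvest score as the baseline for all VAS, ODI and SF-36 efficacy endpoints. There are two candidates:
- **The screening score.** It precedes randomisation and has washout marked. It is also the score nearest to the entry threshold of 40 mm, so it brings more regression to the mean.
- **The score at the bone-marrow visit before extraction.** It precedes the unequal procedure, though possibly not randomisation. If it is chosen, the washout rows of table 6.1, which have no mark in that column, must be reconciled with footnotes a and b. The text should also say that, after a repeat extraction, the score before the first one counts.

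Keep the Day 0 scores for a sensitivity analysis.

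The cost is protocol wording, with no new assessment. The baseline becomes older: 41 to 45 days before Day 0 for screening, 31 to 45 days for the bone-marrow visit, so about 4 to 6 weeks. That adds some noise and regression to the mean, expected equally in both arms.
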